#### Secondary objectives

1) Explore and describe nurse-perceived changes in caring attitudes/behaviours post-intervention (T2); and 2) examine the mediating effects of team cohesion on quality of NPR and nurse QoWL.

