#### Proposed hypotheses

Based on Duffy and Hoskins’ framework [9, 29] and in accordance with the main objectives of this research, we will make the following statistical hypotheses: 1) post-intervention, frequency of nurse caring attitudes/behaviours will be higher in the experimental group (EG) vs a waiting-list control group (WLCG); 2) post-intervention, team cohesion level will be higher in the EG vs the WLCG; 3) post-intervention, level of nurse QoWL will be higher in the EG vs the WLCG; 4) post-intervention, patient-perceived frequency of nurse caring attitudes/behaviours will be higher in the EG vs the WLCG; and 5) post-intervention, level of patient QoL will be higher in the EG vs the WLCG.

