### Data analysis

For the quantitative component of the study described in this protocol, first, we will check the data for inclusion conditions and outliers. Outlying data will be verified individually. Second, associations between factors and outcomes will be described using frequencies, means and standard deviations or medians and interquartile ranges. In addition, these associations will be evaluated using chi-square tests, Fisher tests or analyses of variance. Third, linear regression models adjusted for significant sociodemographic and health variables will be used to examine the intervention’s effect on the different variables selected for the study, keeping in mind that nurse QoWL remains the key outcome variable. Moreover, we will consider a random intercept to take HD unit variance into account. Fourth, we will test whether team cohesion acts as a mediator in the relationship between NPR (independent variable) and nurse QoWL (outcome variable). For this purpose, we will run three regressions: 1) regression of mediator on independent variable (EIIP-70); 2) regression of outcome variable (QoWL) on independent variable; and 3) regression of outcome variable on both independent variable and mediator. Fifth, an intention-to-treat analysis will be conducted of the data on all participants, whether they complete the intervention or not. This will diminish bias related to protocol deviations or withdrawals and will allow estimating the intervention’s effects under conditions that are close to real life. Sixth, based on sample size and sample design (10 HD units of different sizes for a total of 135 nurses) and considering an intra-class correlation coefficient of 0.03 for the HD units, we will be able to detect an effect size of 0.6, with statistical power of 0.8 and significance level at 0.05 for all analyses. The expected effect size has been fixed by the investigators and corresponds to the minimal clinically significant effect. The intra-class correlation coefficient selected is in line with Giraudeau’s recommendations [52] of 0.001 to 0.05 for a cluster RCT. The data will be analysed using the R software [54].

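### The mediation regressions name neither randomised arm nor T0 scores, so stable differences in how nurses rate can pass for mediation by team cohesion

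*Protocol article*

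**What the plan says.** The objective is to "examine the mediating effects of team cohesion on quality of NPR and nurse QoWL" (Secondary objectives). Data analysis sets the path as cohesion mediating "in the relationship between NPR (independent variable) and nurse QoWL (outcome variable"), so the exposure is a questionnaire score and not the randomised arm.

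Three regressions follow, named by their terms: "we will run three regressions: 1) regression of mediator on independent variable (EIIP-70"), QoWL on EIIP-70, and "regression of outcome variable on both independent variable and mediator". This is the fourth step of the analysis. Adjustment for sociodemographic and health variables belongs to the third step, on the intervention's effect, as does the sentence "we will consider a random intercept to take HD unit variance into account". The fourth step repeats neither.

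Proposed hypotheses expects arm to move all three variables:
- NPR: "frequency of nurse caring attitudes/behaviours will be higher in the experimental group (EG")
- cohesion: "post-intervention, team cohesion level will be higher in the EG vs the WLCG"
- QoWL: "post-intervention, level of nurse QoWL will be higher in the EG vs the WLCG"

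Table 2 schedules all three nurse scales at T0, T1, T3 and T4. No visit is assigned to exposure, mediator or outcome. The Theoretical framework section does not settle the order either: it lists cohesion among the upstream structure variables and again as an intermediate outcome beside NPR.

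**The concern.** The third regression reads the cohesion coefficient, given EIIP-70, as the cohesion-to-QoWL leg. That reading fails if anything else drives both. Two such causes can be seen in the document.

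- **Arm.** By the trial's own hypotheses it raises all three scores.
- **The rater.** One nurse answers all three questionnaires, and EIIP-70 is a self-rating. A nurse who tends to score high on everything produces positive correlations among the three without any causal path.

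The T0 scores that would absorb much of the second cause are collected but not named in these models. At stake is a secondary conclusion about how the intervention works: a positive result could not be told apart from a shared rating tendency.

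**Working it through.** **The plan's own figure.** None is given for the mediation test. The stated power of 0.8 concerns an effect of 0.6, and its inputs hang together: design effect 1 + (13.5 − 1) × 0.03 = 1.375; effective sample 135/1.375 = 98.2; power 0.84 with equal arms and 0.82 with a 50/85 split. I use those inputs below.

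**Inputs from the protocol.** 135 nurses in 10 units, ICC 0.03, effect 0.6 SD, two-sided 0.05 (sidedness assumed), at least 50 nurses per arm; 100 nurses in the first data wave (Preliminary results).

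**Assumed.** A stable nurse trait makes up a share τ of each score (0, 0.2 or 0.3). The unit effect is common to the three scales. One post-intervention visit is analysed. There is no path among the three scores. Mediation counts as reported when leg a (EIIP-70 to cohesion) and leg b (cohesion to QoWL given EIIP-70) are both significant. The protocol states no decision rule.

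**By formula.** With equal arms, arm adds 0.6² × 0.25 = 0.09 to each variance and each covariance. With variance 1 before arm:

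- covariance = τ + 0.03 + 0.09; variance = 1.09; r = covariance/1.09
- a = r; b = r/(1 + r); spurious indirect effect = a×b
- t for a = r√(N−2)/√(1−r²); t for b = b√(N−3)/√(1−b²)
- chance of each being significant ≈ Φ(t − 1.96)

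| τ | r | b | a×b | t for a, t for b (N=100) | both significant | t for a, t for b (N=135) | both significant |
|---|---|---|---|---|---|---|---|
| 0 | 0.110 | 0.099 | 0.011 | 1.10, 0.98 | 0.19 × 0.16 = 3% | 1.28, 1.15 | 0.25 × 0.21 = 5% |
| 0.2 | 0.294 | 0.227 | 0.067 | 3.04, 2.30 | 0.86 × 0.63 = 54% | 3.54, 2.68 | 0.94 × 0.76 = 72% |
| 0.3 | 0.385 | 0.278 | 0.107 | 4.13, 2.85 | 0.985 × 0.81 = 80% | 4.82, 3.33 | 0.998 × 0.91 = 91% |

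**By simulation** (3,000 runs per setting, unequal units, constrained allocation, ordinary least squares, stable variance share 0.6 in total):

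| Terms in the models | τ=0, N=100 / 135 | τ=0.2, N=100 / 135 | τ=0.3, N=100 / 135 |
|---|---|---|---|
| as listed | 3% / 5% | 51% / 69% | 79% / 90% |
| + arm | 0.5% / 0.4% | 27% / 42% | 63% / 79% |
| + T0 scores | 5% / 8% | 11% / 20% | 17% / 27% |
| + arm + T0 scores | 0.3% / 0.2% | 0.4% / 0.8% | 1.1% / 1.2% |

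Independent runs with the same structure gave 50–53% and 68–69% at τ=0.2, 78–79% and 89–90% at τ=0.3, and 4–6% at τ=0. If the total effect of EIIP-70 on QoWL must also be significant, the as-listed rates are 44% / 65% at τ=0.2 and 77% / 90% at τ=0.3.

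**Which omission matters.** With 135 nurses, arm alone gives 1.8%, unit alone 0.6% and neither 0.3%, whereas a 20% or 30% trait alone gives 32% or 73%. The trait is the main driver. Arm matters once the trait is present: T0 scores without arm still leave 11–27%.

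**What the covariates cannot repair** (135 nurses, τ=0.2, no cohesion-to-QoWL path). With a same-visit response component shared by the three scales, the false rate is 96% as listed and 96% with unit and T0 terms. With a reverse path from QoWL to cohesion it is 99.9% as listed and 29% with those terms. Ordering the visits and adjusting for QoWL at T3 gives 1.4% and 0.6%.

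**What the fix costs.** With true same-visit legs a = b = 0.3, arm and T0 adjustment still found both legs in 67% and 83% of runs with 100 nurses (τ=0, 0.2) and in 86% and 94% with 135. Replacing the arm term with unit fixed effects gave 60–77% and 81–92%.

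**The case against.** The strongest reply is that the sentence names the paths and does not exclude covariates. Visit choice and covariates for a secondary mediation analysis often wait for an analysis plan, and the random-intercept sentence stands just before and may be meant to carry over. On unit this has force, and unit alone adds almost nothing. On arm and T0 it has less: the regressions are listed term by term, and adjustment is placed in a different step with a different purpose. Run as listed, they give a biased answer.

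Several stronger readings are tempting and not supported:

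- **Mediation would be found whatever the truth.** The high rates depend on an assumed shared trait. Without it they are about 3–6%. The protocol says only that mediation will be examined, and none of its five hypotheses concerns mediation.
- **Leaving out arm is the main fault.** Alone it yields 1.8%.
- **The three regressions yield no indirect effect.** They do: a×b from the first and third, equal to the drop in the EIIP-70 coefficient between the second and third when fitted by least squares to the same data.
- **A fixed T1/T3/T4 sequence must replace the models.** It guards against reverse and same-occasion association, but the six-month lags have no basis in the document and power may be poor. With 100 nurses and true same-visit legs of 0.5, a lagged model with arm and T0 terms found both legs in only 14% (no trait) to 27% (20% trait) of runs.
- **Bootstrap by unit.** Sampling procedure allows as few as 2 units in an arm. With a 2/8 split, 0.8^10 = 10.7% of resamples contain no unit from the smaller arm, and resampling 2 units within an arm gives only three distinct samples.

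**Conclusion.** The point holds. As listed, the mediation models omit arm and the T0 scores, although the trial's own hypotheses make arm a common cause of all three variables and one nurse rates them all. If nurses differ stably in how they rate, the models often show mediation with no path behind it: about 50–70% of trials at a 20% shared trait and about 78–90% at 30%, with 100–135 nurses. Adding arm and T0 scores brings this to about 1–2% or less.

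The size rests on the trait share, which the document neither gives nor allows one to derive, and on a rule that both legs be significant, which is also assumed. Even adjusted models support only an association, because EIIP-70 is not randomised and same-visit scores cannot exclude reverse or same-occasion effects. A reader might infer that the trial's main result is in doubt. It is not: the comparison of arms on QoWL does not use these regressions.

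**What to change.** Amend the fourth step of Data analysis as follows.

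1. Include randomised arm, the T0 values of EIIP-70, GEQ and QoWL, and the unit random intercept in all three regressions, and state which visit or visits are analysed.
2. Report the indirect effect a×b with an interval, for example by Monte Carlo from the estimates and standard errors of a and b, in place of a count of significant steps. Do not prescribe resampling of units.
3. Label the result exploratory and associational, and give the reason: the exposure is not randomised and same-visit measures do not fix direction.
4. Optionally add a time-ordered sensitivity analysis (EIIP-70 at T1, cohesion at T3, QoWL at T4), noting that its power may be low.
5. Word the path in Secondary objectives to match Data analysis.

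The cost is a change of wording plus some power to show a true mediated path. All the data are already scheduled.

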### Ethical considerations

Special attention will be focused on three ethical elements: informed consent (of nurses and patients), confidentiality, and support. Regarding informed consent, the study participation form will provide information on the purpose of the study described in this protocol, the measures to be used to ensure anonymity, and freedom to withdraw from the study at any time without consequence for their professional career in the case of the nurses and for treatment and care received in the case of the patients. Consent forms completed by respondents will be kept in a suitable place for as long as required by the Swiss Ethics Committees on Research Involving Humans. Regarding confidentiality, the names of the respondents will not appear on any form or interview transcript. A code will be assigned to each form and a letter to each establishment. For the purposes of longitudinal follow-up, a password-protected file will be created containing the information necessary to administer questionnaires post-intervention. This file will be destroyed upon completion of the repeated measurement at twelve post-intervention. Regarding support, respondents will be able to reach a contact person throughout the study if they have any questions. They will also be able to access all the study results and/or a summary of the highlights by email, telephone, conventional post or the Moodle interface. The principal investigator will be responsible for drafting the final research report. Researchers have already obtained the required ethics certificate from the Human Research Ethics Review Board of the Canton of Vaud (Switzerland).

### Preliminary results

The inclusion of participants was initiated in September 2017. Currently, we have completed the first wave of data collection, including 140 patients and 100 nurses. The EI has been deployed to all the nurses included in the EG.

## Discussion

Though Watson’s Theory of Human Caring has often been described as a vital guide to humanistic nursing practices, to date, very few studies in the field of nursing have sought to test this disciplinary theory experimentally. Such research is essential as the results obtained would serve to consolidate the theory’s construction and to guide us in improving the EI. By examining the EI’s beneficial effects on both nurses and the HD patients in their care, the study described in this protocol will allow us to gain a better understanding of the EI’s direct effects on nurses’ clinical practice transformation and its indirect effects on HD patients’ QoL over the long term. The results obtained will allow us to bolster the relevance of humanistic practice as a means of ensuring quality of care and patient safety. Continuing professional development activities need to be offered to nurses to this end. The study described in this protocol will help us determine whether the EI in question is effective in this regard.

### Limitations

We are opting for a cluster RCT for fear of contamination between the EG and the WLCG should the two be present in the same unit. As with a conventional RCT, numerous potential factors could compromise the validity of the study described in this protocol and thus bias the results. Uppermost among these are the high risk of participant dropout, among both nurses and patients, owing to the study’s longitudinal design. In order to limit this potential bias, an information letter will be created to keep participating nurses abreast of how the research project is progressing. Moreover, regular contacts between the research team and the head nurses of the different units included in the study will be planned over the entire course of the project. Where the HD patients are concerned, each data collector will take the time to read the questionnaire comprising the different instruments of measure to each patient who manifests the desire to take part in the study. Such a strategy proved effective in the past when used by the principal investigator to collect data from this population [35]. In addition, the research team could have some difficulty implementing the EI if participation translated into a heavier workload for participating nurses. In order to limit this potential bias, all the partnering care institutions will consider the time spent by the nurses engaging in the EI as work time. Also, the institutions will consider the EI as top-priority training for HD units.

## Abbreviations

CF: Carative Factors
CNPI-70: Caring Nurse-Patient Interaction Scale
EG: Experimental Group
EI: Educational Intervention
EIIP-70: French-language version of the Caring Nurse-Patient Interaction Scale
GEQ: Group Environment Questionnaire
HD: Haemodialysis
NPR: Nurse-Patient Relationship
QoL: Quality of Life
QoWL: Quality of Working Life
RCI: Relational Caring Inquiry
RCT: Randomised Controlled Trial
WHOQOL-BREF: World Health Organization Quality of Life scale (short version)
WLCG: Waiting-List Control Group
